### 2.11. Data Collection and Management

A notebook will be created to record the data obtained in an orderly manner for each subject over time, and this data will subsequently be transferred to a unified database designed for this purpose. The samples and associated data will be coded. Therefore, the handling, communication, and transfer of such data will be governed by Organic Law 3/2018 of December 5th, on the protection of personal data and the guarantee of digital rights. Participants may access, correct, or cancel their data at any time. Only the research team and the health authorities, who are duty-bound to maintain confidentiality, will have access to all the data collected by the study, which will be stored securely and guarded by the principal investigator (PI). This study will be conducted in accordance with the Declaration of Helsinki and the rules of Good Clinical Practice. Participants and/or guardians will also be informed that this intervention is not part of the standard service offering and that any subject may withdraw from the study at any time upon request.

## 3. Conclusions

The results obtained from this study will provide valuable information on the changes in weight and key MetS parameters that occur following a nursing consultation designed to prevent and manage this condition in individuals with early-onset psychosis. If the results of this study are positive, the study should be replicated with a larger sample size and with different personnel implementing the intervention.

## Figures and Tables

**Table 1 nursrep-15-00003-t001:** Schedule of enrolment, interventions and assessments.

	Enrolment	Allocation	Post-Allocation							
TIMEPOINT	0	0	w 1	w 3	w 5	w 8	w 12	w 16	w 24	w 48
ENROLMENT:										
Eligibility screen	X									
Informed consent	X									
Allocation		X								
INTERVENTIONS:										
Mental health nurse consultation			X	X	X	X	X	X		
Aims and giving patients handbook			X							
Calorie counting errors and food to avoid				X						
Insulin and fats, proteins and CH					X					
Tips and feeding protocols						X				
Physical activity type							X			
Follow-up and counselling								X		
Treatment as usual										
ASSESSMENTS:										
Weight	X	X	X	X	X	X	X	X	X	X
Anthropometric variables (height, blood pressure, lab test…)			X						X	X
Scales (PANSS, HAM-D, EQ-5, IPAQ)			X						X	X

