## 2. Methods

### 2.1. Design

This protocol is designed as an open-label, randomized clinical trial involving a group of patients in a first-episode psychosis (FEP) program, who will attend a series of nursing consultations focused on healthy habits aimed at addressing metabolic syndrome, in addition to their usual follow-up. The control group will consist of patients from the same program who will attend only routine nursing evaluation consultations.

The first author ([name]) will conduct the nursing consultations, based on a previously developed guide that structures and serves as a reference framework for the intervention.

This study was retrospectively registered on Clinical Trials—NCT06650943.

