### 2.4. Randomization and Treatment Allocation

Subjects will be selected during their psychiatry consultations following the stabilization of their pathology. If they meet the inclusion/exclusion criteria, they will be informed about the possibility of participating in the study, including its content and purpose. After being provided with an informed consent form and signing it, they will be randomly assigned to either the experimental or control group. Randomization will be conducted using a computer-generated random list. As participants are offered the opportunity to join the study, they will be assigned a number from the list in sequential order. The psychiatrist who refers the participants will not have access to the randomization list, ensuring allocation concealment. On the other hand, the psychiatrist responsible for administering the psychometric scales will be blinded to the intervention.

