### 2.5. Intervention

The study intervention will consist of a series of 8 nursing consultations with a specialized mental health nurse, who is trained in teaching healthy habits to individuals with psychosis and understands the unique factors influencing this group. The nurse will also be skilled in using the therapeutic relationship as a tool for habit modification.

During the first two months, 4 consultations will be held, focusing on educating patients about dietary habits based on the carbohydrate–insulin theory of obesity and physical activity, following a manualized intervention previously designed by a team composed of a mental health nurse, a nutrition and dietetics graduate, and a psychiatrist. This guide has been designed based on the consensus report of the American Diabetes Association for nutrition therapy for diabetes and prediabetes [26], as well as incorporating insights from clinical experience with individuals with a first episode of psychosis. The next two visits will take place 3 and 4 months after the first visit, respectively. Visit 7 will be held after 6 months to evaluate the intervention’s effectiveness, and visit 8 at 12 months. During all visits, weight will be monitored as a reinforcement element.

At the beginning of the study, and at 6 and 12 months from the start of the intervention, a battery of tests will be conducted, including analytical samples, vital signs, anthropometric measurements, and scales to assess psychopathology, quality of life, and level of physical activity.

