As shown in Table 1, each consultation will have a central topic. The first session will cover the objectives of the intervention, emphasizing the achievement of greater well-being and the prevention of various cardiometabolic illnesses. The second session will explain the importance of food quality over calorie counting. In the third session, patients will be educated on identifying different macronutrients, their functions, and the relationship between insulin and weight regulation. The fourth session will provide various tips and types of diets to help patients incorporate this model into their own situations. The fifth session will focus on physical activity, highlighting the most efficient types for fat loss and the improvements that patients can implement. The sixth consultation will involve a follow-up to assess any difficulties in making changes and refine strategies to overcome them. After this consultation, the intervention will be concluded. The overall approach will focus on the progressive and flexible acquisition of habits, aiming to integrate changes into the patient’s daily life. This will occur within the therapeutic relationship established between the mental health nurse and the patient, utilizing a psychoeducational and non-blaming approach.

The consultations will use a previously developed guide, which will be provided to patients to allow them to review the information discussed during the sessions.

To improve adherence to the intervention protocol, participants will be called by phone two business days before their visits.

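### The only baseline for the scales, blood pressure, waist and laboratory values is scheduled at week 1, after open-label allocation, which puts mainly the EQ-5D and IPAQ change comparisons at risk

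*Protocol article*

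**What the plan says.** Section 2.1 sets the design: "This protocol is designed as an open-label, randomized clinical trial". Section 2.4 goes directly from consent to assignment, with no baseline battery between them: "After being provided with an informed consent form and signing it, they will be randomly assigned to either the experimental or control group". Section 2.5 times the test battery thus: "At the beginning of the study, and at 6 and 12 months from the start of the intervention". It does not say whether the first battery comes before allocation.

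Table 1 does state the timing. The rows "Scales (PANSS, HAM-D, EQ-5, IPAQ" and "Anthropometric variables (height, blood pressure, lab test" have their first mark at w 1, under the post-allocation heading. The rows "Mental health nurse consultation" and "Aims and giving patients handbook" also start at w 1. Of that first visit Section 2.5 says: "The first session will cover the objectives of the intervention, emphasizing the achievement of greater well-being". Weight is the only measurement marked at enrolment and at allocation.

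Waist circumference is not named in the table row, but Section 2.7 lists it among the anthropometric variables, so it is read here as part of that row.

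**The concern.** A baseline should be something the allocation cannot have influenced. Once participants know their arm, a measurement is a post-randomisation variable, even if it is taken before any treatment content is delivered. Section 2.8 compares changes in the outcomes between groups over time with a repeated-measures model. If w 1 is the first time point in that model, any arm difference already present at w 1 enters the change contrast.

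The measures concerned carry all the stated secondary aims: metabolic parameters, psychopathology, physical activity and quality of life. Two of them, EQ-5D and IPAQ, rest on what the participant reports. In the intervention arm they are collected in the same week as a session that stresses well-being.

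**Working it through.** The plan states no figure on this point, so the check is a reading of the schedule followed by an illustrative calculation.

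**Step 1. Columns of Table 1.**

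| Row | Enrolment (0) | Allocation (0) | w 1 | w 3 to w 16 | w 24 | w 48 |
|---|---|---|---|---|---|---|
| Consent | X | | | | | |
| Allocation | | X | | | | |
| Nurse consultation | | | X | X (five) | | |
| Weight | X | X | X | X (five) | X | X |
| Anthropometry, blood pressure, laboratory | | | X | | X | X |
| Scales | | | X | | X | X |

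The alignment can be trusted. The weight row fills all ten columns, and the six consultation marks run from w 1 to w 16, matching the six sessions in Section 2.5. As w 24 and w 48 are the follow-ups, w 1 is the only possible baseline for the last two rows.

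**Step 2. Does the text place the battery earlier?** No. Section 2.4 has consent and then assignment. The wording in Section 2.5 is compatible with w 1.

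**Step 3. Which measures can move?**
- EQ-5D and IPAQ: the participant's own report, with the arm known. This is the main exposure.
- PANSS and HAM-D: Section 2.4 says the psychiatrist who administers the psychometric scales is blinded. The participant is not, so the risk is smaller but not nil.
- Laboratory values and blood pressure: the w 1 session covers aims and hands over the booklet. Specific dietary content starts at w 3 and the physical-activity session is at w 12. An effect is probably negligible.

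**Step 4. Size, under assumptions.** Let δ be the arm difference at w 1 caused by knowing the arm, in SD units. Let ρ be the baseline–follow-up correlation, with equal SDs at both times.
- Bias of a change-score contrast: δ in absolute size.
- Bias of a baseline-adjusted contrast: ρ × δ.

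Neither δ nor ρ is in the documents. With δ = 0.2 and ρ = 0.5, and with δ halved and doubled:

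| δ (SD) | Change score | Adjusted, ρ = 0.5 |
|---|---|---|
| 0 | 0 | 0 |
| 0.1 | 0.1 | 0.05 |
| 0.2 | 0.2 | 0.1 |
| 0.4 | 0.4 | 0.2 |

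At δ = 0.2, varying ρ from 0 to 1 moves the adjusted bias from 0 to 0.2.

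For scale, take the 74 analysable participants of Section 2.9 as 37 per arm. At ρ = 0.5 a change has SD √(2 − 2 × 0.5) = 1. The standard error of the change-score contrast is then √(2/37) = 0.23 SD, and 0.2/0.2325 = 0.86 standard errors. The adjusted contrast has standard error 0.2325 × √(1 − 0.5²) = 0.20 SD, and 0.1/0.2013 = 0.50 standard errors.

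**The case against.** The strongest reply is that measuring after allocation biases a comparison only if allocation changed the measurement. The order of events within w 1 is not given, so the battery may come before the first session. The label may simply mean the first study week, close to time 0: Section 2.5 puts visits five and six at 3 and 4 months after the first visit, and the table labels them w 12 and w 16. This stands against any claim that bias is certain. It does not remove the point, because a battery taken before the session would still follow open allocation.

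A reader might also infer that the primary outcome is compromised, since weight is marked at enrolment, allocation and w 1, and Section 2.8 does not say which one is the reference for the 5% rule. The documents do not support this. Weight is scheduled at time 0 for all participants without distinction by arm, and nothing suggests that the arms would use different reference weights. Naming the reference weight is a clarification only.

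A further inference is that controls have their baseline in a different setting, because Section 2.6 gives them no specific nursing consultations. Section 2.1, however, has them attend routine nursing evaluations, and Section 2.5 does not limit the battery to one arm. The difference is possible but not shown.

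**Conclusion.** The point holds for the secondary outcomes. Table 1 fixes their only baseline after open-label allocation and in the week of the first consultation, and no other section corrects this. Because the schedule states the timing, it is not a detail left to a fuller document.

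The consequence is a possible bias in between-arm comparisons of change, concentrated in EQ-5D and IPAQ. At the assumed 0.2 SD shift it would be below one standard error of the contrast: enough to distort an estimate, but not a large effect. Its direction cannot be told from the documents. Comparisons of follow-up values that do not use the w 1 measurement are untouched, and the primary weight outcome is not shown to be affected. It is worth correcting because the remedy is simple.

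**What to change.** In both arms, set the order as consent, baseline battery, allocation, first consultation. In Table 1, move the w 1 marks of the scales row and of the anthropometry, blood pressure and laboratory row to the enrolment column. Amend Section 2.5 to say that the first battery precedes allocation. As a clarification, state in Section 2.8 that the reference for the 5% rule is the last weight before allocation.

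The trial was registered retrospectively, so recruitment may have begun. If participants are already enrolled under the current schedule, apply the change to new participants and report which baseline timing each participant had.

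The cost is modest. The tests are the same, and sample size and follow-up do not change. Allocation must wait until the battery, including the fasting sample, is complete, which may need an extra visit. A few people may be tested and then not allocated.

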## Data Availability

No data are available as this manuscript presents a study protocol.
